### 2.3. Eligibility Criteria

Trained psychiatrists/psychologists will review the diagnosis of depression using the Brazilian version of the Mini International Neuropsychiatric Interview 5.0.0 (MINI) [19], which was developed based on the *Diagnostic and Statistical Manual of Mental Disorders*, 4th edition (DSM-IV) and International Classification of Diseases and Related Health Problems, 10th revision (ICD-10). 

Inclusion criteria are: (a) age between 18 and 60 years; (b) diagnosis of major depressive disorder or depressive episode in bipolar disorder according to DSM-IV; (c) baseline HAMD17 score ≥17; (d) current TDR episode; (e) appropriate clinical condition for receiving ECT as assessed by a psychiatrist and an anesthesiologist; and (f) meeting transcranial magnetic stimulation (TMS) safety criteria [20]. In the definition of TRD for major depressive disorder, the utilization of a minimum of two prior treatment failures will be considered. Conversely, for TRD in bipolar depression, only one prior treatment failure will be required. In both cases, there must be confirmation of prior adequate dose and duration, based on clinical criteria evaluated using the Antidepressant Treatment History Form (ATHF) [21,22].

Exclusion criteria are: (a) pregnancy; (b) psychiatric comorbidity (except mild anxiety disorders); (c) depressive symptoms better explained by other clinical conditions or psychiatric disorders; (d) decompensated clinical and neurological conditions or serious sequelae of previous medical conditions; (e) use of psychoactive substances in the last 6 months (except nicotine); (f) use of monoamine oxidase inhibitors in the last 6 months; (g) application of ECT or another neuromodulation technique in the last 12 months; (h) contraindications for ECT or MRI; (i) relevant deviations in clinical laboratory parameters; or (j) inability to consent.

Discontinuation criteria are: (a) worsening depression; (b) development of suicidal ideation or suicide attempt; (c) withdraw consent; (d) development of (hypo)manic symptoms; (e) inability to induce seizures lasting at least 15 s after adjusting parameters and medications during the titration phase; (f) missing two consecutive treatment sessions; or (g) changes in drug treatment without the previous authorization.

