#### 2.4.3. MST

The MagVenture MagPro MST with Twincoil (Magventure, Farum, Denmark) will be used for MST sessions. The procedure will follow the same guidelines as ECT sessions regarding general anesthesia, oxygenation, motor activity monitoring, EEG, and postictal recovery. The Twin Coil will be centered over point Fz of the 10–20 system using an EEG cap to mark the correct point on the patient’s scalp.

The stimulation will be delivered with an amplitude of 100%, 100 Hz. In the first session, a titration of the convulsive threshold will be performed with a 2 s stimulus (200 pulses). If an adequate seizure is not triggered, the stimulus will be increased by two seconds (200 pulses) until a seizure is triggered or a maximum of 3 to 4 attempts is reached. If a seizure is not initiated in the first session, a new titration session will be scheduled. Medication will be reviewed and, if possible, the dose of benzodiazepines will be reduced depending on the opinion of the performing psychiatrist. The second titration session will repeat the same process as the first, with the parameters used in the last attempt. The maximum limit is set at 10 s of stimulation or until the coil temperature exceeds the safety limit. If no seizure is triggered in the second session, the patient will be excluded from the study. In subsequent sessions, the stimulus used will be 4 s (400 pulses) higher than the titration session, up to a maximum of 1000 pulses. If the patient has seizures of less than 20 s duration, the number of pulses will be increased by 200 pulses in the next session, until the seizures are effective or the limit of 1000 pulses is reached. These parameters were determined based on our previous experience [30].

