### 2.9. Statistical Analysis

Statistical analyses will be performed in R. The results will be considered statistically significant only if both conditions are met, that is, non-inferiority for the depression outcome, under unilateral *p* < 0.025, and superiority for the cognitive outcome, under *p* bilateral < 0.05. The following groups will be considered: experimental (E), corresponding to MST, and control/comparison (C), corresponding to ECT.

For the co-primary outcome depression (HAMD17), non-inferiority will be assessed by calculating the difference between the means of groups E and C and its 95% confidence interval at the end of the 12th session, which will then be compared to the NI margin (Ha: C-E < NI). Analyses will be performed on modified intent-to-treat (ITT) samples (at least 8 sessions of ECT/MST) and per-protocol (PP).

For the co-primary cognitive outcome (AMT [32]), we will perform linear hierarchical model analyses using a first-order regressive covariance structure, which includes all observed variables without the need to enter data for missing values. The dependent variable is the AMT score [32], the independent variables are time (all observations through week 6) and group. We will test the statistical significance of this interaction according to our superiority hypotheses controlled for age, years of schooling, and treatment-resistant depression (Ha: C-E < 0). Analyses will be performed on the ITT and PP sample.

The same linear hierarchical models will be used for all continuous secondary outcomes. We will assess response and sustained remission, that is, a clinical improvement of symptoms ≥50% (response) and a HAMD17 score ≤7 (remission) at a given point in the study, which will be maintained until the outcome. The trajectories of response and sustained remission between groups will be compared using Kaplan–Meier survival analysis. Response and remission will be compared considering non-inferiority margins of 20% and 15%, respectively. The choice of a 15% non-inferiority margin was based on the consideration that achieving a remission rate of 35% holds clinical relevance in this population with difficult-to-treat depression. Furthermore, this remission rate surpasses those achieved by more conventional and less invasive treatment options for TDR, such as repetitive TMS (rTMS) with an approximate remission rate of 20% [66] and antidepressants with a remission rate of 14% [1].

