### 2.10. Sample Size Calculation

The software programs G * Power 3 [67] from Universität Düsseldorf, Germany, and Stata (Statacorp, College Station, TX, USA) were used to conduct calculations. The sample size was determined using parameters of α = 0.025 (one-tailed), β = 0.2, and a standard deviation of 9.5. The margin of non-inferiority (NI) was determined based on a combination of statistical reasoning and clinical judgment [68]. The lower bound of the confidence interval from a meta-analysis comparing ECT vs. sham was used to establish the NI [69]. Using a meta-analysis by the UK ECT Review Group [16], the difference in HAMD17 scores between ECT and placebo was 9.7 points (95% CI 5.7 to 13.5), with an NI value of 5.7. Despite the large margin, this NI value was deemed acceptable due to the cognitive effects of bitemporal ECT (the control comparison). Thus, MST would be a reasonable non-inferior intervention, as cognitive superiority would also need to be demonstrated. The sample size required was 88 patients, with an additional enrollment of 10% (total of 100 patients, 50 per arm) to account for attrition. For the superiority analysis, we used data from an unpublished clinical trial of 75 patients that compared the efficacy and cognitive outcomes of MST vs. ECT (personal communication from [name]). The effect size of AMT [32] after 12 treatment sessions was approximately 1.31, requiring a sample size of 26 patients to demonstrate a difference. Thus, the larger sample size from the clinical outcome study was used for the NI calculation.

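### Kaplan–Meier for response and sustained remission needs a rule for outcome-related exits: censoring or dropping them overstates the proportion of randomised patients who respond or remit

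*Protocol article*

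**What the plan says.** Section 2.9 sets the method: "The trajectories of response and sustained remission between groups will be compared using" Kaplan–Meier. Response and remission are defined by HAMD17 thresholds reached "at a given point in the study, which will be maintained until the outcome". The section then adds: "Response and remission will be compared considering non-inferiority margins of 20% and 15%, respectively". It does not say whether the margin comparison uses the Kaplan–Meier estimates or simple proportions, which analysis set applies to these outcomes, or how patients who leave early are handled. The modified intention-to-treat set of at least 8 sessions is stated for the HAMD17 co-primary outcome.

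The exit rules are elsewhere. Section 2.3 begins its list: "Discontinuation criteria are: (a) worsening depression; (b) development of suicidal ideation or suicide attempt". It goes on to include (hypo)manic symptoms and failure to induce an adequate seizure during titration. Section 2.2 confirms that patients whose depression worsens leave the study. For failed titration section 2.4.3 states: "If no seizure is triggered in the second session, the patient will be excluded from the study". Section 2.4.2 has the same rule for ECT.

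The only related figure is in section 2.10, where the required 88 patients are raised "with an additional enrollment of 10% (total of 100 patients, 50 per arm) to account for attrition".

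**The concern.** A Kaplan–Meier curve for a favourable event estimates the proportion who will have had the event if those censored keep the same chance of it as those still at risk. A patient removed for worsening, suicidality, (hypo)mania or failed seizure induction no longer has that chance on the allocated treatment. Censoring such a patient passes the lost weight to those who stay, so one minus Kaplan–Meier (1−KM) is larger than the proportion of randomised patients who respond or remit. Dropping the patient from the analysis set has the same effect.

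The response and remission rates in each arm are at stake, and they are among the results a clinician will read first. The contrast between arms is also at stake if exits are unequal. Unequal exits are possible because the two techniques have different titration steps and output limits.

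**Working it through.** **The plan's own figure.** No figure is given for the Kaplan–Meier analysis. The sample size on which the attrition allowance rests does reproduce: 2 × (1.96 + 0.84)² × 9.5² / 5.7² = 43.6, so 44 per arm and 88 in total. A 10% allowance gives 88 / 0.9 = 97.8, so 98; the plan rounds to 100, leaving 12 of 100 as spare.

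**Inputs for the check.** These are 50 patients per arm (section 2.10), margins of 20% and 15% (section 2.9), and exit proportions and remission rates. The article gives no exit rate or expected remission rate by arm, so those are assumptions. Failure exits q are set at 6% and 12%; the upper value treats all the spare enrolment as treatment failure. Remission r among those who stay is set at 35, 50 and 65%.

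**Size within one arm, exits before the first rating.** This fits failed titration, which precedes the first on-treatment HAMD17 (after session 6, Table 1). With censoring or exclusion the estimate is r. The proportion of randomised patients who remit is (1 − q) × r. The standard error (SE) is √(p(1 − p)/50), where p is that proportion.

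| q | r (estimate) | (1 − q) × r | Excess | Excess / SE |
|---|---|---|---|---|
| 12% | 35% | 30.8% | 4.2 points | 0.64 |
| 12% | 50% | 44.0% | 6.0 points | 0.85 |
| 12% | 65% | 57.2% | 7.8 points | 1.1 |
| 6% | 35 to 65% | 32.9 to 61.1% | 2.1 to 3.9 points | 0.32 to 0.57 |

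**Size with exits spread over three ratings.** Assume conditional remission of 0.15, 0.35 and 0.30 at the session-6, post-12 and post-18 ratings, with 4% of those still at risk leaving before each.

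- 1−KM = 1 − 0.85 × 0.65 × 0.70 = 61.3%.
- Cumulative incidence = 0.96 × 0.15 + 0.816 × 0.96 × 0.35 + 0.509 × 0.96 × 0.30 = 0.144 + 0.274 + 0.147 = 56.5%.
- The excess is 4.8 points, or 0.69 SE.

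**Between arms.** Section 2.9 supports its 15% margin by saying that "achieving a remission rate of 35% holds clinical relevance in this population with difficult-to-treat depression". Adding the margin implies about 50% on ECT, which is an inference and not a stated value. Take true proportions among all randomised of R = 50% on ECT and 35% on MST, a true deficit of 15 points. With a proportion d leaving, early exits give an estimate of R / (1 − d). Exits spread at constant hazard give 1 − exp(−L × R / (R + d)), where L = −ln(1 − R − d).

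| Exits MST / ECT | Apparent deficit, early exits | Apparent deficit, spread exits |
|---|---|---|
| 10% / 10% | 55.6 − 38.9 = 16.7 points | 16.2 points |
| 20% / 5% | 52.6 − 43.7 = 8.9 points | 11.8 points |
| 5% / 20% | 62.5 − 36.8 = 25.7 points | 21.6 points |

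The bias can therefore run either way. With early exits it favours MST only once MST exits exceed ECT exits by about 2 to 4 points (7% against 5%, or 14% against 10%).

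**If the margin comparison used such estimates.** This was simulated with 50 per arm, a 15-point margin, a Wald 95% interval and 200,000 runs, at a true deficit equal to the margin. Non-inferiority was declared in 8.4% of trials with early exits of 20% on MST and 5% on ECT, against 2.3% when the same patients count as non-remitters. With 10% exits in each arm the figures were 1.7% and 2.2%.

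**The case against.** The strongest reply is that the article states no censoring rule. An article condenses the full protocol, and the rule may be in a document that is not shown. Kaplan–Meier also does not force the wrong handling, since failures can be kept at risk without an event to the end of follow-up within the same method. Both points are right, and they limit the finding to what happens under the default. Part of the concern remains because the plan names a method whose ordinary use goes wrong under the plan's own exit rules.

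A second reply is that failed titrations might not enter at all, if the 8-session set also applies here. That would not remove the problem. Dropping early failures from the denominator leaves remission among those who stay, which is the same inflation.

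Third, (hypo)mania and adverse events are compared separately by chi-square. That reports one type of failure but does not correct the response and remission rates.

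Fourth, the assumed sizes may be high. The 6% and 12% are not observed failure rates, and the exits in section 2.3 also include consent withdrawal, missed sessions and unauthorised drug changes, which need not be failures. At 6% the excess is mostly below about half an SE. This stands and is why a range is given.

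A reader might infer that the method hides a higher failure rate on MST and so favours non-inferiority. The article does not support this. It gives no exit rate by arm, applies the same exclusion rule to both techniques, and does not say that the margins are tested on Kaplan–Meier estimates. With equal exits and truly lower remission on MST, the bias runs against MST.

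**Conclusion.** The point holds in a limited form. If outcome-related exits are censored or dropped, response and remission are overstated relative to all randomised patients by about 2 to 8 points per arm. This rests on assumed failure exits of 6 to 12% and remission of 35 to 65% among those who stay. The contrast between arms is distorted when exits differ, in a direction that cannot be known from the article. Any effect on the 20% and 15% margins depends on the further assumption that they are assessed on the same estimates.

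Only secondary outcomes are concerned. Trial success rests on the HAMD17 means and the Autobiographical Memory Task, and neither uses Kaplan–Meier. The matter is still worth settling before data are seen, because these comparisons carry stated margins and the unknown direction leaves room for a choice made after the fact.

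**What to change.** In section 2.9:

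- State that response and sustained remission are analysed in all randomised patients.
- Treat exits for worsening, suicidal ideation or attempt, (hypo)mania and failed seizure induction as competing events, and report the cumulative incidence (Aalen–Johansen). Equivalently, keep these patients at risk as non-responders to the end of planned follow-up.
- For the 20% and 15% margins, count the same patients as non-responders or non-remitters and use the confidence interval for the difference in proportions.
- If the curves are compared, Gray's test is suitable, but it tests equality and does not establish non-inferiority.
- State how the remaining exits (consent withdrawal, missed sessions, unauthorised drug changes) are handled, and report all exits by reason and arm.

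The cost is wording, since section 2.3 already defines the exit reasons. The downside is that the stated response and remission rates will be lower. Nothing here changes the exit rules themselves.

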### 2.1. Study Design, Setting, and Recruitment

The study involves a double-blinded, randomized, non-inferiority clinical trial [14] with two treatment arms (see Figure 1: study design) conducted at the Institute of Psychiatry, Hospital das Clínicas, São Paulo, Brazil.

Recruitment will be conducted through referrals from physicians in the ECT Service (mainly from the Institute of Psychiatry), self-referral via university community advertisements (e.g., leaflets and email), and advertisements on the website (www.sin.org.br), Google, and social media platforms such as Facebook.

After the recruitment and selection process, participants will undergo a baseline assessment, which includes medical evaluation, neuropsychological assessment, laboratory tests, and cranial MRI. They will then be divided into two groups (ECT and MST). The study will utilize a 1:1 controlled randomization model with blocks of random sizes and lengths generated through www.sealedenvelope.com.

Generally, during the acute phase of ECT, the frequency of treatment sessions varies from one to three times per week. Studies have indicated that ECT conducted twice a week shows comparable efficacy to ECT performed three times a week, while requiring a reduced number of treatments. Additionally, there appears to be greater efficacy of ECT applied three times a week compared to the weekly application schedule [15]. Regarding cognitive functioning, the more frequent the sessions, the greater the cognitive impairments [16]. Consequently, we have opted to conduct ECT or MST sessions during the active phase with a frequency of twice a week on non-consecutive days.

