### 2.8. Seric Biomarkers

Venous blood collections will be performed in the morning, fulfilling a minimum fasting period of 8 h comprising the following events:C1 (Collection 1): Performed on the day corresponding to the first session, prior to the procedure, taking advantage of the need for venipuncture. This will be considered the baseline sample;C2 (Collection 2): performed prior to 6th session;C3 (Collection 3): performed prior to 12th session;C4 (Collection 4): performed prior to 18th session (if any);C5 (Collection 5): performed 12 weeks after the start of the treatment;C6 (Collection 6): performed 24 weeks after starting treatment, coinciding with the 3-month medical evaluation.

Two 4 mL tubes of venous blood samples with anticoagulant (EDTA) will be collected before each event to prevent biochemical alterations related to the convulsive crisis. The collections will be performed at the ECT Service and immediately transported to the Neuroscience Laboratory LIM-27 for proper storage until the biochemical analysis is conducted. Post-treatment collections (C5, C6, and C7) will be scheduled with the staff and patient at the Neuroscience Laboratory LIM-27 after an 8 h fast. Brain-derived neurotrophic factor (BDNF) will be evaluated in the plasma using an immunofluorescence ELISA technique, which is highly specific for this type of evaluation. This technique has been shown to be more appropriate for state-dependent assessment of BDNF levels than other methods [61].

Our primary objective is to explore potential associations between changes in plasma BDNF levels and variations in depressive symptom scores and treatment response, as well as other clinical and neuroimaging outcomes (such as the variation in volume of each ROI). Additionally, we intend to compare the differences in plasma BDNF variation over time in patients undergoing ECT or MST. Moreover, we will evaluate the discrepancies in BDNF levels between patients who respond positively to treatment and those who do not, in each treatment arm.

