Based on previous studies [62,63,64,65], our hypothesis is that there will be a progressive increase in plasma BDNF levels, especially in the subgroup of patients with lower BDNF levels at baseline. We also hypothesize that there will be a positive correlation between improvement in depressive symptoms and an increase in BDNF, but its significance will be observed specifically in relation to plasma BDNF collected at time points C5 and C6. Additionally, we believe that higher baseline plasma BDNF levels may be associated with higher rates of treatment response and remission and, possibly, better cognitive outcomes. Furthermore, there will be a similar increase in plasma BDNF levels in patients who undergo ECT when compared to those who receive MST.

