We will define adverse events as events with intensity greater than “mild” and at least “remotely” associated with the intervention, as carried out in our previous studies [31]. The presence of adverse events and (hypo)manic upset will be compared between groups E and C using the chi-square test. This test will also be used to assess whether allocation group guessing occurred beyond chance.

Regarding the BDNF data, each collection during the follow-up will be individually analyzed in relation to the baseline values using Student’s *t*-test. The same analysis will be conducted to assess the differences between the treatment groups (ECT x MST) at each endpoint. Additionally, analysis of variance (ANOVA) will be used to evaluate potential differences in the means of plasma BDNF at different collection time points. A significance level of 5% will be adopted for all tests.

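### The between-arm t-tests on BDNF, whether on levels or on change from C1, do not use C1 as a covariate and so give up precision that costs nothing to recover

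*Protocol article*

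**What the plan says.** Section 2.8 of the protocol article sets the between-arm aim in terms of change: "we intend to compare the differences in plasma BDNF variation over time in patients undergoing ECT or MST". Of C1, drawn before the first session, it says: "This will be considered the baseline sample". It also states a hypothesis for the contrast: "there will be a similar increase in plasma BDNF levels in patients who undergo ECT when compared to those who receive MST".

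Section 2.9 gives the BDNF method in three steps.

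- Within patients, "each collection during the follow-up will be individually analyzed in relation to the baseline values using Student’s" t-test.
- Between arms, "The same analysis will be conducted to assess the differences between the treatment groups (ECT x MST) at each endpoint".
- Across time, "analysis of variance (ANOVA) will be used to evaluate potential differences in the means of plasma BDNF at different collection time points".

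It adds: "A significance level of 5% will be adopted for all tests". No BDNF analysis names C1 as a covariate, and the ANOVA names no arm term.

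The same section also has a general rule that continuous secondary outcomes are analysed with the linear hierarchical models described for the autobiographical memory outcome. The covariates listed there are age, years of schooling and treatment resistance. No baseline biomarker value is among them.

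**The concern.** The aim is differential change, and a baseline sample is planned for every patient, yet the named between-arm test leaves out the covariate likely to explain most of the outcome variance. The wording allows two readings.

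- **Levels.** The two-sample t-test compares BDNF at each collection. It does not estimate change from C1, and a chance C1 difference carries into the result in proportion to r.
- **Change from C1.** C1 is subtracted in full. When r is below 1 this over-corrects, so a chance C1 difference enters with the opposite sign. When r is below 0.5 the change test is less precise than the level test.

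The trial was sized for HAMD17, and no BDNF power, SD or correlation is given. The stake is a noisier estimate of the difference in BDNF between the two treatments, one that also depends on how the arms happened to fall at C1.

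**Working it through.** **Inputs from the protocol article.** Section 2.10: 88 patients required, 100 enrolled (50 per arm), one-sided alpha 0.025, power 80%, SD 9.5, margin 5.7. Section 2.1: "The study will utilize a 1:1 controlled randomization model". Section 2.9: 5% level for BDNF, sidedness not stated.

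**Assumptions.** Two-sided 5%; equal SDs in both arms and at both times; r = 0.3 to 0.8; an illustrative true difference of 0.5 SD.

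**1. The plan's own figure.** n per arm = 2 × (1.960 + 0.842)² × 9.5² / 5.7² = 43.6, rounded up to 44, or 88 in total. The stated figure is reproduced. I use 44 per arm as the analysed number.

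**2. Variance of the between-arm difference**, in units of 2·SD²/n:

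- levels: 1
- change from C1: 2(1 − r)
- adjusted for C1: 1 − r²

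Adjusted relative to levels is therefore 1 − r². Adjusted relative to change is (1 − r²) / [2(1 − r)] = (1 + r)/2. Both ratios are below 1 whenever 0 < r < 1.

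| r | adjusted / level | adjusted / change |
|---|---|---|
| 0.3 | 0.91 | 0.65 |
| 0.5 | 0.75 | 0.75 |
| 0.7 | 0.51 | 0.85 |
| 0.8 | 0.36 | 0.90 |

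**3. Power.** Noncentral t, 44 per arm, with standardised differences 0.5 (levels), 0.5/√[2(1 − r)] (change) and 0.5/√(1 − r²) (adjusted):

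| r | level | change | adjusted |
|---|---|---|---|
| 0.3 | 64% | 50% | 68% |
| 0.5 | 64% | 64% | 76% |
| 0.6 | 64% | 74% | 83% |
| 0.7 | 64% | 85% | 90% |
| 0.8 | 64% | 96% | 97% |

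**4. Chance imbalance at C1.** The standard error of the C1 difference is √(2/44) = 0.213 SD, so 5% of trials will show a difference beyond 1.96 × 0.213 = 0.42 SD. A C1 difference of b shifts the level estimate by r·b and the change estimate by −(1 − r)·b. The adjusted estimate is not shifted. For b = 0.20 SD, the level shift is +0.06, +0.10 and +0.14 SD at r = 0.3, 0.5 and 0.7, and the change shift is −0.14, −0.10 and −0.06 SD.

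With no true difference, and only within that 5% of trials, simulation gives these false-positive rates:

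| r | level | change |
|---|---|---|
| 0.3 | about 10% | about 24% |
| 0.6 | about 25% | about 16% |
| 0.8 | about 44% | about 10% |

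Over all trials, both t-tests hold 5% and both estimates average to the true difference.

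**The case against.** **C1 may already be used.** The between-arm sentence follows one that analyses each collection against baseline, and the aim in Section 2.8 is about variation over time. A change-score test is at least as natural a reading as a level test. A reader might infer that the plan ignores C1 altogether; the text does not support that. What stands is that subtracting C1 is not the same as adjusting for it, and the loss of precision remains for any r below 1.

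**The t-test is valid.** A reader might take the 44% figure as the plan's error rate. It applies only to the level reading, at r = 0.8, in the 5% of trials with a large C1 difference. Under the change reading the matching figure is about 10%. This is conditional error and loss of efficiency, not systematic bias.

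**The gain is uncertain.** This is correct. Against the level test at r = 0.3, power rises only from 64% to 68%; against the change test at r = 0.8, from 96% to 97%. The 0.5 SD difference is illustrative, and because the hypothesis is one of similar increases, these powers show relative precision only and are not the power for that hypothesis.

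**Another analysis may be planned.** A reader might infer that these t-tests are the only between-arm comparison of BDNF. The general rule in Section 2.9 makes that insecure: if BDNF counts as a continuous secondary outcome, a group-by-time model applies. Against this, the BDNF paragraph sets its own method, and Section 3 lists the biomarkers apart from the secondary outcomes. The rule would not by itself supply the adjustment. With C1 as one of the outcomes, arm means free at baseline, time as categories and complete data, the contrast in change from C1 is essentially the change-score difference.

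**This is detail for an SAP.** Covariates often are left to one. Here, though, the article itself names the test.

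**Conclusion.** The point holds as one of efficiency. Under either reading, the named t-test is valid on average but less precise than a C1-adjusted comparison. Over r = 0.3 to 0.8, adjustment reduces the variance by 9% to 64% against the level test and by 35% to 10% against the change test. The size rests on the assumed r and on equal SDs; the direction holds for any r between 0 and 1. Importance is low, because BDNF is a secondary or exploratory biomarker and neither co-primary conclusion depends on it.

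**What to change.** Replace the between-arm t-tests in Section 2.9 with one C1-adjusted comparison, chosen in advance from:

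- analysis of covariance of BDNF on arm and C1 at each collection scheduled for all patients (C2, C3, C5 and C6); or
- a mixed model with arm-by-visit terms and C1 as covariate.

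The two are not interchangeable when samples are missing, so the text should name one. Report the adjusted difference with its 95% confidence interval.

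Treat C4 as descriptive. It is taken only before an 18th session, so it comes only from patients not in remission after session 12. That group is selected after randomisation, and adjusting for C1 does not restore comparability.

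State whether the hierarchical-model rule for continuous secondary outcomes covers BDNF, so that the two parts of Section 2.9 agree.

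The cost is a few sentences of analysis text and about one degree of freedom. C1 is already scheduled for every patient, so no new data are needed. The change is best made before BDNF results are seen.
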